## Abstract

**Background:**

Cesarean section is an important surgical procedure, when normal vaginal delivery imposes a risk to mother and/or baby. The World Health Organization states the ideal rate for Cesarean section to be between 10 and 15% of all births. In recent decades, the rate has been increased dramatically worldwide. This paper explains the protocol of a randomized controlled trial that aims to compare the effect of “motivational interviewing” and “information, motivation, and behavioral skills” counseling interventions on choosing mode of delivery in pregnant women.

**Methods:**

A four-armed, parallel-design randomized controlled trial will be conducted on pregnant women. One hundred and twenty women will be randomly assigned to four groups including three intervention groups and one control group. The intervention groups included the following: (1) motivational interviewing; (2) face-to-face information, motivation, and behavioral skills model; and (3) information, motivation, and behavioral skills model provided using a mobile application. The inclusion criteria include being literate, being in gestational age from 24 to 32 weeks, being able to speak Persian, having no complications in the current pregnancy, having no indications for Cesarean section, and having enough time to participate in the intervention. The primary outcome of the study is the mode of delivery. The secondary outcomes are women’s intention to undergo Cesarean section and women’s self-efficacy.

**Discussion:**

The interventions of this protocol have been programmed to reduce unnecessary Cesarean sections. Findings may contribute to a rise in normal vaginal delivery, and the effective intervention may be extended for use in national Cesarean section plans.

**Trial registration:**

Iran Randomized Clinical Trial Center IRCT20151208025431N7. Registered on December 07, 2018.

## Administrative information

The order of the items has been modified to group similar items (see http://www.equator-network.org/reporting-guidelines/spirit-2013-statement-defining-standard-protocol-items-for-clinical-trials/).

## Introduction

### Background and rationale {6a}

Cesarean section (CS) is an important surgical procedure, when normal vaginal delivery (NVD) imposes a risk to mother and/or baby [1]. The World Health Organization (WHO) states that a rate of CS between 10 and 15% of all births is ideal; however, the rate is steadily growing in recent years [2]. The average worldwide rate of CS is 18.6%, ranging from 6.0 to 27.2% in the least and more developed countries, respectively. Countries with the highest CS rates are Brazil (55.6%) and Dominican Republic (56.4%) in Latin America and the Caribbean. Iran and Turkey (47.9% and 47.5%, respectively) have the highest rates in Asia [3]. In Iran, the rate is even higher in private hospitals (72–89%) [4–7].

CS can save the lives of mothers and infants in emergency situations. However, current rates suggest that the CS is now used for women with normal and non-complicated pregnancies and births, when it is not medically necessary [8]. Unnecessary CSs could create complications with no benefits to both mother and baby [3, 9–12]. According to an observational study conducted by the WHO in nine Asian countries, women who undergo an unplanned CS before or during labor or who have an assisted (operative) vaginal delivery are more likely to experience morbidity than those who have spontaneous vaginal delivery [13]. As with any surgery, CS is associated with short- and long-term risks that may be minor or severe [14]. CS can be associated with significant short-term risks such as asphyxia, if the uterus is hypoperfused due to anesthesia, scalpel lacerations, and neonatal respiratory morbidities [9]. Other short-term risks of CS include increased risk of infection and lower likelihood of breastfeeding [10, 11, 15]. Moreover, urinary catheterization is associated with post-CS bacteriuria and has been reported to be as high as 11% [16]. Increasing rates of CS are associated with increased maternal and perinatal morbidities [17].

In 2014, Iran’s “health sector evolution policy” was launched to improve public health. One important objective of this policy was to decrease the rate of unnecessary CSs [18]. Several strategies have been conducted such as freeing NVDs in all public hospitals, developing mother-friendly hospitals, developing standard protocols of birth and preparation classes for women, improving privacy and infrastructure of labor, promoting standards in birth facilities, promoting water birth, and determining financial incentives to doctors to encourage them to do NVDs in public hospitals [19]. There was a reduction in CS rate after implementing the policy; however, the rate is still significantly higher than the rate recommended by the WHO [19].

Several studies have been conducted on reasons behind the high rate of CS in Iran [20–23]. Studies have shown that the main reason is the willingness of women to undergo CS due to fear of pain during labor and childbirth [21, 24, 25], concerns about genital modifications after vaginal delivery [26–28], belief that CS is safer for the baby [29–31], and the convenience for women and their families [18]. Studies show that women can play a major role in the decision-making process about their birth [32–36].

In recent years, different interventions intended to reduce the CS rate in Iran [37–40]. Although these interventions have been effective in the short term, they have not been effective in the long term. To further reduce the rate of CS, it is necessary not only to address the health system, health facility, and health professional factors, but also to change women’s choice behaviors [19]. The WHO has provided recommendations on non-clinical interventions to reduce unnecessary CSs. The recommendations are grouped according to the target of intervention: (a) interventions targeted at women, (b) interventions targeted at healthcare professionals, and (c) interventions targeted at health organizations, facilities, or systems [41].

Regarding non-clinical interventions on reducing unnecessary CS targeted at women, the WHO has recommended implementing psycho-education interventions for women [8, 42]. A Cochrane review conducted by Chen et al. on non-clinical interventions for reducing unnecessary CS reported that psycho-education interventions were effective in reducing unnecessary CSs [43]. The educational interventions included psycho-education on fear of childbirth [44], intensive group therapy (cognitive-behavioral therapy and childbirth psycho-therapy) [45], psycho-education by telephone [46], role-play education versus standard education using lectures [47], and nurse-led applied relaxation training program [44].

Several psycho-educational models and methods/strategies have been introduced to change behaviors effectively. Motivational interviewing (MI) is a patient-centered counseling approach to motivate individuals to change their behaviors [48], and it is specifically designed to enhance motivation to change among patients not ready to change [49]. It highlights the importance of motivation in personal behavior change. Research on MI has demonstrated positive effects of helping patients clarify goals, explore obstacles to treatment, and make commitments to change [49]. MI is a relatively new cognitive-behavioral technique that aims to help patients identify and change behaviors that may be placing them at risk of developing health problems or may be preventing optimal management of a chronic condition.

In the Information-Motivation-Behavioral skills (IMB) model, preventive behavioral skills represent a final common pathway for predicting complex preventive behaviors [50]. The IMB model is a generalizable and simple model to guide thinking about complex health behaviors. The IMB constructs, and how they pertain to patient adherence, are outlined below: (1) *Information* is the basic knowledge about a medical condition that might include how the disease develops, its expected course, and effective strategies for its management; (2) *Motivation* encompasses personal attitudes towards the adherence behavior, the perceived social support for such behavior, and the patients’ subjective norms or perceptions of how others with this medical condition might behave; and (3) *Behavioral skills* include ensuring that the patient has specific behavioral tools or strategies necessary to perform the adherence behavior such as enlisting social support and other self-regulation strategies.

In recent years, mobile applications play an important role in delivering educational content. People carry their mobile phones with themselves wherever they go, so educational interventions can be delivered at any time to anyone with extra support upon request wherever and whenever it is needed. This opportunity provides simple and non-expensive interventions to various ranges of individuals. Motivational messages, monitoring, and behavior change tools can be modified for delivery via mobile phones [51]. The effectiveness of this type of intervention is affirmed in several studies such as smoking cessation [52], adherence to prescribed medication [53], and blood pressure management [54]. This paper explains our study protocol aiming at comparing the effect of MI and IMB, and IMB based on mobile application (IMB-App) on choosing the mode of delivery in pregnant women.

### Objectives {7}

This is the protocol of our study that aims at comparing the effect of IM, IMB, and IMB-App counseling interventions on choosing the mode of delivery in pregnant women.

### Trial design {8}

This study is a randomized controlled, parallel-design trial.

## Methods: participants, interventions, and outcomes

### Study setting {9}

Pregnant women will be chosen from private hospitals located in Tehran. We have chosen private hospitals, because they support elective CS by providing high-quality facilities for women. Only in private hospitals, women are able to choose CS as a mode of delivery (maternal request) [18].

### Eligibility criteria {10}

#### Inclusion criteria

The criteria for entering women are being literate, being in gestational age 24 to 32 weeks, being able to speak Persian, having no complications in the current pregnancy, having no indications for CS, and having enough time to participate in the interventions.

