#### Exclusion criteria

We exclude women who show complications during the study, have preterm labor, and are reluctant to continue to participate in this study.

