### Intervention description {11a}

The content of interventions will be designed based on a qualitative evidence synthesis and a quantitative systematic review and meta-analysis in Iran [55]. Also, we will design the interventions tailored to the participants’ needs. The interventions are expected to take around 2 months to be completed, and women will be followed up until their delivery time.Motivational interviewing (MI)In this intervention group, pregnant women will be trained face-to-face based on the MI. During three 45–60-min sessions, MI techniques will be provided to the participants. MI is a directive, client-centered counseling style for eliciting behavior change by helping clients to explore and resolve ambivalence. It is most centrally defined not by technique but by its spirit as a facilitative style for interpersonal relationships. MI is a relatively simple, transparent, and supportive talk therapy based on the principles of cognitive-behavior therapy. In this group, we will help women to explore and resolve ambivalence about the mode of delivery and build their intrinsic motivation.We will not force women to choose a specific mode of delivery. We will ask open-ended questions (for example, “Tell me what you think about CS?” or “What do encourage you to choose this type of delivery (CS or NVD)?”). Open-ended questions can help us to understand how they are thinking about the mode of delivery. Affirming is one of the fundamental MI skills. We will use it to support engagement, encourage the women to further explore change processes, and build confidence. We will find an opinion the client is making or a strength she will notice and reflect it to her (for example, “So how did you manage to control your fear after attending our training sessions?”). We will use reflective listening as a simple method to reduce resistance in MI. The last step of this technique is to summarize what the pregnant women have said.Information, motivation, and behavioral skills model through a face-to-face approach (IMB)During three 45–60-min sessions, the model’s strategies will be provided to the participants. Participants will receive information and behavioral skills related to the choice of mode of delivery as well as internal and external motivational factors related to the choice of delivery. The strategy includes the following: (1) *Information*—the intervention will begin with information on the prevalence of CS and CS-related complications in women, and outcome of unnecessary CS; (2) *Motivation*—the interventionist will perform this technique to motivate pregnant women, providing personal feedback, asking open-ended questions, affirming desirable behavior, reflective listening, working at the women’s pace, and negotiating goals that will be realistic and attainable; and (3) *Behavioral skills*—women will be given behavioral skills training on how to control the obstacle of NVD. To build skills for choosing the mode of delivery, training will be given on how to reduce these barriers.Information, motivation, and behavioral skills model through mobile app (IMB-App)The mobile application (M-health) has been designed based on the IMB model. The software will be installed on mobile phones of participants in the group, and its operation will be taught individually. Women will work with the application in the presence of the research team, and any existing problems will be resolved. The strategies foreseen for adherence improvement include reminders set at defined intervals in the form of pop-up messages. To monitor adherence, the data collected on the server will be used. In addition to the application, a server will be designed in which the users’ activities will be collected. Items such as the duration of application usage and the sections used by the user (in addition to registering their time and duration) will be registered. Every time the user’s mobile is connected to the Internet, the data will be uploaded and saved on to the server. These data can be used as a proxy of adherence to the intervention.

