### Recruitment {15}

We will be present in the research setting during the intervention period to recruit all eligible women. The study will be available to all pregnant women interested in participating and speaking Persian. Individuals who fulfill the inclusion criteria will receive a description of the study, indicating the follow-up schedule and assurance of confidentiality, and they will be directed to complete a consent form. Included participants will be randomly allocated in three intervention groups and one control group.

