## Assignment of interventions: allocation

### Sequence generation {16a}

The participants will be randomly assigned to four groups after the initial assessment and upon completing the baseline data form. We will recruit the participants based on the registration order of women with the clinic, and no other factor will contribute to participants’ order on the list. Each participant on the list will be assigned a consecutive research identification number according to the order by which they will be registered with the clinic. The first participant on the list will be randomly assigned to the MI intervention group, and the next two participants will be assigned to the IMB and IMB-App interventions, respectively. The fourth participant will be assigned to the control group.

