## Data collection and management

### Plans for assessment and collection of outcomes {18a}

The primary outcome of the intervention (mode of delivery) will be measured using a checklist after the childbirth.

The secondary outcomes will be measured by a questionnaire 1 month after the interventions.

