## Statistical methods

### Statistical methods for primary and secondary outcomes {20a}

Data will be analyzed using descriptive statistics (mean, frequency, and standard deviation); inferential statistics including independent *t* test, paired *t* test, chi-squared, and one-way ANOVA tests; and logistic regression modeling to examine the factors affecting the women’s choice on the mode of delivery to examine the simultaneous effect of variables on the chances of choosing CS. The significance level of the tests will be considered as less than 0.05.

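### Baseline intention and parity are recorded before allocation but have no stated role in the primary comparison, which gives up precision at 30 per arm

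*Protocol article*

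**What the plan says.** All references are to the protocol article.

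- **Entry.** The inclusion criteria end with "having no complications in the current pregnancy, having no indications for CS, and having enough time to participate in the interventions". The exclusion criteria are likewise silent on intention: "We exclude women who show complications during the study, have preterm labor, and are reluctant to continue to participate in this study". Under Recruitment {15}: "The study will be available to all pregnant women interested in participating and speaking Persian".
- **Baseline data.** The Questionnaire section lists number of births and a single item on intention. Data management {19} says follow-up uses the same questionnaires as baseline. Sequence generation {16a} has women "randomly assigned to four groups after the initial assessment and upon completing the baseline data form". Both variables are therefore in hand before allocation.
- **Primary outcome.** "The primary outcome of the intervention (mode of delivery) will be measured using a checklist after the childbirth".
- **Analysis.** Section {20a} lists t tests, a chi-squared test, one-way ANOVA and "logistic regression modeling to examine the factors affecting the women’s choice on the mode of delivery". The sentence goes on to the joint influence of variables on the chance of choosing CS. It names no covariates and does not say which analysis gives the primary arm effect. Additional analyses {20b} are marked as not applicable.
- **Size.** 120 women, 30 per arm, with 80% power for a difference that is not quantified.

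**The concern.** A woman's own intention is likely to be among the strongest predictors of whether she has a CS in a hospital where CS can be chosen. Parity is a natural second predictor. When such a predictor is known before allocation, leaving it out of the primary comparison leaves explainable variation in the error term. With 30 women per arm there is little information to spare.

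The protocol describes its logistic model as a study of factors affecting choice, not as the source of the arm effect. As written, the natural primary comparison is therefore the unadjusted chi-squared test. What is at stake is power and the width of the interval, not the validity of the test.

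**Working it through.** **The plan's own figure.** The sample size cannot be reproduced, because no control rate, difference or test is given. Working backwards at 30 per arm, two-sided 5%, 80% power needs CS to fall from 72% to 36.6% (about 35 points) or from 89% to 57.6% (about 31 points). The 72–89% range is the private-hospital CS rate in Background and rationale {6a}. Precision is therefore scarce.

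**Assumptions (no intention data in the documents).** Share intending CS 0.75; CS in 0.90 of them and 0.30 of the rest without counselling; a 30-point fall among intenders and none among the rest. One arm against control, n = 30 each.

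1. *Overall rates.* Control: 0.75×0.90 + 0.25×0.30 = 0.75, inside 72–89%. Intervention: 0.75×0.60 + 0.25×0.30 = 0.525. Difference: 0.225.
2. *Unadjusted.* SE = √[(0.75×0.25 + 0.525×0.475)/30] = √(0.4369/30) = 0.1207. Power ≈ Φ(0.225/0.1207 − 1.96) = Φ(−0.10) ≈ 46%.
3. *Adjusted for intention.* Only variance within intention groups remains. Control: 0.75×0.90×0.10 + 0.25×0.30×0.70 = 0.1200. Intervention: 0.75×0.60×0.40 + 0.25×0.30×0.70 = 0.2325. SE = √(0.3525/30) = 0.1084. Power ≈ Φ(0.225/0.1084 − 1.96) = Φ(0.12) ≈ 55%.
4. *Weaker link (85% against 45%).* The overall rates are again 0.75 and 0.525, so unadjusted power is unchanged. Within-group variances are 0.1575 and 0.2475, SE = √(0.405/30) = 0.1162, and power ≈ Φ(−0.02) ≈ 49%.

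Simulation of the chi-squared test against the adjusted logistic model agrees: about 45% against 56% in the first case and 44% against 48% in the second. Part of the simulated gain arises because the likelihood-ratio test is slightly liberal at this size.

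**Is the unadjusted test valid?** With the same rates and no effect, 2,000 simulated trials with random allocation gave 5.05% rejections by chi-squared, so the error rate is held.

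**Chance imbalance.** With a 75% share, two arms of 30 differ in that share by at least 10 points with probability 0.46 and by at least 20 points with probability 0.10. At a 72% share these are 0.47 and 0.11; at 89%, 0.30 and 0.02. A 20-point gap moves the CS difference by 0.20×0.60 = 12 points. This is not an extra error. With no effect, the variance of the unadjusted difference is 2×0.75×0.25/30 = 0.0125 (SE 11.2 points). The part due to imbalance in intention is 0.60²×2×0.75×0.25/30 = 0.0045, or 36% of it. The unadjusted standard error already contains that part; adjustment removes it.

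**The case against.** **The covariate list may lie elsewhere.** This is a condensed article, no analysis plan is shown, and the logistic model is multivariable, so baseline intention may already be meant to enter it. That limits the point to *no use is stated*. It does not remove it: the article assigns the logistic model to exploring factors and leaves the primary arm comparison without adjustment, although a better analysis is available from data already collected.

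**The gain is modest and assumed.** This stands. The no-effect approximation 1/(1 − 0.36) = 1.56 would suggest a gain worth 56% more women. With the effect present, the variance ratio from the working is 0.4369/0.3525 = 1.24, and in the weaker case 0.4369/0.405 = 1.08.

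**A reader might infer that women planning vaginal birth should be screened out.** The protocol does say of motivational interviewing that "it is specifically designed to enhance motivation to change among patients not ready to change", and of that arm that "we will help women to explore and resolve ambivalence about the mode of delivery". These describe one of three active arms. The sample question in {11a} addresses a preference for either mode, the IMB arms train women to deal with obstacles to vaginal birth, enrichment by setting is already built in, and the Abstract looks to national CS plans. Broad entry is defensible. No effect among women planning vaginal birth is an assumption; counselling might keep some of them from switching to CS.

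**A reader might also infer that chance imbalance makes the result unreadable as an effect on choice.** The working shows otherwise: the error rate holds, and the imbalance is already counted in the standard error.

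**Conclusion.** The point holds as one of efficiency. Two likely prognostic variables are recorded before allocation, and the article states no use of either in the primary comparison. Under the assumed rates, power is about 45% unadjusted and 56% adjusted for intention; with the weaker link the gain is about 4 points (44% to 48%). Any further gain from parity has not been quantified. The size rests wholly on assumed intention and CS rates.

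The validity statement assumes allocation that behaves as random; the fixed rotation described under Sequence generation {16a} is a separate matter. The documents do not support calling the unadjusted result biased or uninterpretable, nor calling the entry criteria wrong. Adjustment also does not undo dilution. If only intenders respond, their 30-point effect is 0.75×30 = 22.5 points overall, and only an estimate by baseline intention would show the difference.

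**What to change.** In section {20a}, name as the primary analysis of mode of delivery the arm effect from the planned logistic model, adjusted for baseline intention to undergo CS and for parity (any previous birth). Because the ordinary likelihood-ratio test runs slightly liberal at 30 per arm, use a small-sample-robust method, such as penalised likelihood or a permutation test, or report the adjusted risk difference with its interval. Keep the chi-squared test as a secondary, unadjusted result. Report the arm effect by baseline intention as a supportive estimate, without a claim of its own.

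The cost is wording, with no new data and no change to eligibility. One detail must be settled first: the Questionnaire section gives no response format for the intention item, so its coding as a covariate, and the grouping for the supportive estimate, need to be fixed before outcome data are seen.
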